### Clinical parameters

The pain numerical rating scale (NRS) is a pain self-assessment tool. The patient rates his or her pain orally on a scale from 0 to 10, where 0 corresponds to the lower limit defining absence of pain and 10 corresponds to the upper limit defining the worst imaginable pain. The NRS was preferred to a VAS (visual analogue scale) based on the 2009 expert consensus on cancer pain assessment [44].

This scale can be used to include patients considered to experience sufficiently severe pain to justify more or less invasive treatment. For example, pain scored as 3/10 corresponds to moderate pain [45, 46], which should be controlled by global management and/or the use of mild analgesics (WHO step 1 [47]). Pain scored between 7 and 10/10 is considered to be major pain (between severe and maximum) [45]. Pain scored as 4/10 is considered to be moderate, but with a significant impact on the patient’s quality of life [48] and needs to be treated by noninvasive or minimally invasive modalities (WHO step 2 or 3 analgesics or noninvasive brain stimulation techniques, including tDCS). Invasive treatments (e.g. cervical cordotomy [49] or implantable pumps for intrathecal drug administration [50]) specifically intended for palliative care patients can be considered in patients experiencing pain with NRS scores higher than 6–7/10 and could be proposed in the event of failure of tDCS in the context of this protocol.

The validity and reliability of the NRS for the evaluation of the efficacy of analgesic treatment has been established [45]. A 20 to 30% improvement of the NRS score is generally considered to be significant [51]. This percentage improvement appears to be sufficient to assess the efficacy of a drug treatment associated with few adverse effects [52]. A higher level of efficacy (≥ 40% improvement) is generally required for surgical treatment in view of the higher risks involved. Various authors have considered that a noninvasive interventional treatment, such as tDCS, can be evaluated according to the same criteria as drug treatments [53, 54]. In the more specific field of palliative care, a 2-point improvement on NRS was estimated to be significant in 74.3% of cases in a group of 70 patients treated with ketamine infusion [55]. In 2 other reported cases, again in the palliative care setting, ketamine infusion resulted in a 2 and 3 point decrease in NRS, respectively, accompanied by clinical improvement deemed sufficient to allow the 2 patients to return home [56]. These results were the basis for our study’s enrollment calculations. Also in palliative care, it has been established that an assessment of pain, using only a scale such as the NRS was insufficient [57]. For this reason, the following scales were added to the study of clinical parameters.The Brief Pain Inventory (BPI) is a self-administered questionnaire constructed and tested in cancer pain [39]. It explores the main dimensions of pain: site, intensity, functional impairment, social repercussion, interpersonal relations and psychological distress. It will be used in this trial, as in most clinical trials.

The short form, composed of 9 items, has been validated and shown to be reliable in the assessment of cancer pain [38]. The BPI and its short version were validated in French in 2007 [58]. In palliative care, the BPI has been recommended for the assessment of adult patients without cognitive impairment [57]. It has been reported that some patients may have difficulty performing this assessment alone [59]. Our protocol concerns hospitalized patients who will all be assisted to complete the questionnaires.Evaluation of the various symptoms observed in the context of palliative care constitutes an evaluation of the quality-of-life approach in this setting. The Edmonton Symptom Assessment System (ESAS) has been validated and found to be one of the most reliable of the various scales [40]. This scale is relatively easy to score by drowsy and/or tired patients, in contrast with questionnaires like the McGill Quality of Life Questionnaire [60] or VOICES-SF [22]. ESAS evaluates 9 symptoms by means of a visual analogue scale (0–100 mm): pain, tiredness, nausea, depression, anxiety, drowsiness, lack of appetite, shortness of breath and wellbeing. In general, mean scores between 10 and 30, 40 and 60, and 70 and 100 mm reflect slight, moderate and severe discomfort, respectively [61].Since 1983, anxiety and depression are generally evaluated by the HADS (Hospital Anxiety and Depression Scale [41]). The HADS has been validated and recommended to evaluate these symptoms in the context of cancer pain and palliative care [62].The STAI-Y [42] is a self-administered questionnaire designed to study the state of anxiety experienced at a given point in time in adults and is composed of 20 questions, scored from 1 to 4.

Scores range from 20 to 80 and are classified in the following way:very high > 65,high: 56 to 65,moderate: 46 to 55,low: 36 to 45,very low ≤35.

To date, this scale has not been validated for the evaluation of cancer pain, nor in the context of palliative care. As much as an improvement of a possible depressive state could be explained by the action of the tDCS [63], it is not at all known that the tDCS can have a proper effect on anxiety. Anxiety may, however, contribute to the distress that can be encountered in a palliative care setting. A recent publication suggests that tDCS may have an effect on this state of distress [64], which highlights the interest of an own assessment of anxiety.The Medication Quantification Scale (MQS) is a scale used to quantitatively evaluate changes in analgesic drug administration [37]. Each medication is attributed a score corresponding to a class of drugs, mainly taking their adverse effects into account. Daily doses are also classified as a function of recommended dosages. The total score is the product of the score corresponding to the drug class and the score corresponding to its daily dose. This score has been used in 3 studies in palliative care patients treated by noninvasive transcranial brain stimulation techniques [13–15]. In this context, it proved to be reliable, its evolution reflecting well the clinical evolution of the 3 treated patients.

### Statistical analysis

Statistical justification of the sample size: a 2-point improvement of the numerical rating scale is considered to be clinically relevant [51], which is supported by data from the study conducted by Cheung [55] on the efficacy of ketamine in a population of patients in palliative care setting (see “Clinical Parameters”).

As this is the first protocol dedicated to the treatment of painful patients in a palliative care setting with tDCS, we did not find any evidence in the literature that could help us justify the number of needed patients for the evaluation of the other clinical parameters, apart from the NRS.

On the basis of these hypotheses:A mean NRS difference of 2 points between the active tDCS arm and the sham tDCS arm,Standard deviation of 2.8,Power of 80%.Alpha risk of 5%,

32 patients per arm would be necessary, i.e. a total of 64 patients. In order to ensure sufficient power, an additional 10% of patients will be included in the study, i.e. a total of 70 patients.

The study will therefore include 70 patients: 35 in the tDCS arm and 35 in the sham tDCS arm.

The variables measured on inclusion will be described for all patients and in each of the two arms by number and percentage for each modality for qualitative variables and by minimum, maximum, mean, standard deviation and quartiles for quantitative variables. The primary efficacy population will be a modified intention-to treat (mITT) population, comprising all randomized patients who have received at least one tDCS session (active or sham) and who were evaluated on D0 (baseline) and on D8.

#### Analysis of the primary endpoint

Analysis of the primary endpoint, the pain NRS, will be performed on the mITT population.

The mean NRS score on D8 will be compared between the active tDCS arm and the sham tDCS arm using a mixed linear model in order to take stratification factors into account.

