### Study objective

This study is designed to evaluate the analgesic efficacy of 5 consecutive tDCS sessions to the primary motor cortex in patients with cancer pain in the palliative care setting.

The primary endpoint is the score of the numerical rating scale (NRS), which measures pain intensity on a scale from 0 to 10 [36]. The mean of 3 NRS scores recorded during the day (morning, midday and evening) will be used. The primary endpoint for analysis will be the mean variation of the pain NRS between the baseline assessment (D0) and the D8 assessment.

The secondary objectives will be to evaluate:Immediate impact of each tDCS session on pain intensity.Response rate at the end of treatment.Residual analgesic effect.Effects of TDCS on the other main symptoms likely to impair quality of life.Analgesic consumption on D0 and D8.

Secondary endpoints will be:Pain NRS score, MQS (Medication Quantification Scale [37]), including evaluation of opioid consumption expressed in oral morphine equivalent per day on D0 and D8.Pain NRS scores, recorded before and after each session.Efficacy of treatment, defined by a ≥ 20% reduction of the mean NRS score between D0 and D8 (IMMPACT recommendation in chronic pain [38]).Mean NRS score on D14 and D21 in the 2 arms.Completion of the following questionnaires and scales on D0 and D8:. BPI (Brief Pain Inventory, short form [39]).. ESAS (Edmonton Symptom Assessment System) [40].. HADS (Hospital Anxiety and Depression Scale) [41].. STAI-Y (State-Trait Anxiety Inventory (Form Y) [42]).Analgesic consumption assessed by MQS on D0 and D8.

Analysis of repeated measurements of quantitative secondary endpoints (NRS, BPI, ESAS, HADS, STAI-Y and MQS) will be based on the mean variations of the endpoint between the baseline assessment (D0) and the D21 assessment.

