#### Inclusion criteria

Patients between the ages of 18 to 80 years with cancer pain refractory to medical treatment (mean NRS ≥ 4/10 on 2 consecutive days) in the palliative care setting.Patients agreeing to participate in a research protocol in this palliative care setting.

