### Study plan (Fig. 1)

#### Screening visit (D-3)

Verification of inclusion and exclusion criteria. Patients will be provided with the information sheet and will be asked to sign the informed consent form. The patient will be provided with NRS forms (3 assessments per day for 48 hours). For organizational reasons, this screening visit will be held on a Friday. NRS scores will be recorded on Saturday and Sunday so that inclusion or exclusion of the patient can be decided on Monday.

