### Randomization

Centralized randomization will be performed on D0 after verification of the inclusion criteria. Randomization will be performed under double-blind conditions and will be stratified according to the mean baseline pain intensity (4–6 or 7) over the last 48 hours before inclusion and according to centre.

Patients will be randomized to receive either active tDCS or sham tDCS for the 5 treatment days defined by the protocol. The randomization ratio will be 1:1. Randomization will be stratified by centre by means of the Ennov Clinical electronic CRF (https://fr.ennov.com/getions-essais-cliniques/) by logging onto the website: https://nantes-lrsy.hugo-online.fr/CSOnline/ after obtaining the patient’s informed consent on D0. The inclusion number and randomization arm will be automatically allocated at the time of randomization. A confirmation e-mail will be sent to the person who performed randomization and to all other people concerned.

Randomization lists will be established by a Nantes university hospital research promotion department statistician.

A patient registered in the trial, to whom treatment has been allocated and documented, will be considered to be randomized. A patient cannot be included, evaluated or randomized in the trial more than once.

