One of the limitations of this protocol is the lack of a pilot study, which led us to make choices that were not always well documented in the development of the protocol. The first choice was to select the tDCS system best suited for a double-blind treatment protocol in a palliative care setting. There are now several devices available that meet these criteria well. The HDC Kit makes it easy to perform double-blind stimulation easily at the patient’s bed. The calculation of the number of patients could not be based on similar protocols. Those dedicated to cancer pain [17, 18] were aimed more at non-hospitalized patients with a priori a life span of more than 3 months. The only protocols performed in palliative care involved ketamine infusion treatments. Since we were dealing with the same population and in principle the same expectations (in particular the return home), we chose the same main criterion, which was NRS improved by at least 2 points. The date of the “end point” was also chosen in a way that is open to discussion. It would have been possible to choose D4 which corresponds to the date of the 5th day of treatment. This date also corresponds to the date of maximum improvement in a case we have previously treated [15]. However, there is almost always a post-effect that should allow patients to be stimulated sequentially, for example 5 days in a row every 10 or 15 days, which would be easier to perform in routine. Therefore, it was the evaluation of the quality and duration of the aftereffect that led us to choose D8 as the “end point” date.

We hope that this protocol will be able to confirm the value of tDCS in the treatment of cancer pain in palliative care patients, especially by facilitating a rapid return home.

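### The primary endpoint is defined as change in NRS from D0 to D8, but the primary analysis compares D8 means with baseline pain only as a two-level stratum, and that stratum leaves means between 6 and 7 unclassified

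*Protocol article*

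**What the plan says.** All places are in the protocol article.

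- **Endpoint.** The Study objective section states: "The primary endpoint for analysis will be the mean variation of the pain NRS between the baseline assessment (D0) and the D8 assessment". The abstract and the Figure 1 legend also word the primary objective as an improvement from baseline to D8.
- **Analysis.** The section on analysis of the primary endpoint states: "The mean NRS score on D8 will be compared between the active tDCS arm and the sham tDCS arm using a mixed linear model". The stated purpose of the mixed model is to allow for the stratification factors. Neither a change score nor baseline NRS as a covariate is named.
- **Strata.** The Randomization section says that allocation is "stratified according to the mean baseline pain intensity (4–6 or 7) over the last 48 hours before inclusion and according to centre".
- **Source of the baseline mean.** The screening visit section says: "The patient will be provided with NRS forms (3 assessments per day for 48 hours", which is six scores. Entry requires "mean NRS ≥ 4/10 on 2 consecutive days".
- **Which baseline.** The abstract places it between D-3 and D-1, the Study objective section at D0, and the Figure 1 legend between D-3 and D0.
- **Sample size.** The Statistical analysis section assumes "A mean NRS difference of 2 points between the active tDCS arm and the sham tDCS arm" and "Standard deviation of 2.8", with 80% power and 5% alpha, giving 32 per arm. It does not say whether 2.8 is the SD of D8 scores or of change.

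**The concern.** The article names both a variable and a model for the primary question, and they differ. This is therefore not a detail left to an analysis plan. Change and D8 score estimate the same between-arm difference in a randomised trial, but in one data set they can give different estimates and p-values. Nothing in the article says which one counts.

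Baseline NRS is collected, and the mITT definition requires it for every analysed patient. Reducing it to two levels discards information about the D8 score.

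The stratum definition matters twice: it decides which randomisation list a patient joins, and it is the only route by which baseline pain reaches the primary model. A cut that does not cover every eligible value leaves both uncertain.

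**Working it through.** **1. The plan's own figure.** Difference 2, SD 2.8, two-sided 5% alpha, unadjusted two-sample t-test, noncentral t: 31 per arm gives 79.0% and 32 per arm gives 80.3%. The stated 32 is reproduced. It needs no baseline adjustment.

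**2. Precision under three uses of baseline.** The documents give no baseline–D8 correlation r, so r = 0.3, 0.5 and 0.6 are assumed, and 2.8 is read as the SD of D8 scores. Residual SDs:

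- D8 score unadjusted: 2.8.
- Two-level stratum: 2.8·√(1 − c²r²), where c is the correlation of the stratum with continuous baseline. A normal baseline split in half has c² = 2/π, so c ≈ 0.80.
- Continuous baseline: 2.8·√(1 − r²).

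For r = 0.5 the stratum gives 2.8·√(1 − 0.637·0.25) = 2.57, and continuous baseline gives 2.8·√0.75 = 2.42. Power at 32 per arm (noncentral t, ignoring the few degrees of freedom spent on covariates):

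| r | Unadjusted D8 | Two-level stratum | Continuous baseline |
|---|---|---|---|
| 0.3 | 80.3% | 82.6% | 83.9% |
| 0.5 | 80.3% | 86.6% | 90.1% |
| 0.6 | 80.3% | 89.3% | 94.0% |

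The stratum gives up about 1, 3.5 and 5 points. With baselines simulated as truncated normals on 4–10 and cuts at 6, 6.5 and 7, c was mostly 0.77 to 0.82. In the least favourable case it was 0.66 (few patients above the cut). There, at r = 0.5, the residual SD is 2.8·√(1 − (0.664·0.5)²) = 2.64 and power is 84.7%, a loss of about 5 points.

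**3. D8 or change as response.** Write Y for D8 NRS and B for baseline. If Y = a + τ·arm + βB + strata + e, then Y − B = a + τ·arm + (β − 1)B + strata + e. The arm effect τ, its standard error and its p-value are the same in both, provided that the B subtracted is the B used as covariate.

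**4. The gap in the strata.** A mean of six whole-number scores moves in steps of 1/6. The values 6.17, 6.33, 6.50, 6.67 and 6.83 lie neither in 4–6 nor at 7 or above. If the printed 7 is meant literally, means above 7 are unclassified too. To size the gap, six rounded scores per patient were simulated with patient mean 5.5–7, between-patient SD 1.5–2 and within-patient SD 1 (all assumed), keeping means of at least 4. Between 17% and 22% of eligible patients fall strictly between 6 and 7. Rounding truncated-normal baselines (mean 5.5–6.5, SD 1.2–1.5) to sixths gives 22–23%.

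**The case against.** The strongest reply is that nothing is invalid. Randomisation makes the D8 comparison unbiased for the same between-arm difference, the 32 per arm is right for it, and the planned stratum adjustment can only raise power above 80%. The precision loss is relative to a better model, and its size depends on a correlation that the documents do not give. All of this stands, and it limits the point to a mismatch and an avoidable inefficiency.

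On the strata, a sign before the 7 may have been lost in the text, and the electronic system may apply a fixed or rounding rule. The article does describe automatic allocation, so it would be wrong to say that patients are classified ad hoc. The printed definition still does not cover 6.17 to 6.83 with the sign restored.

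Three stronger readings are tempting but not supported:

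- **A plain change score would cost much power.** Taking the SD of change as 2.8·√(2(1 − r)) gives 66% power at r = 0.3. That needs a baseline SD of 2.8. Entry confines the baseline mean to 4–10, where the largest possible SD is 3.0 (half the patients at each end) and a uniform spread gives 6/√12 = 1.73. The simulation in step 4 gives 1.2–1.6. With baseline SD 1.4, the SD of change at r = 0.3 is √(2.8² + 1.4² − 2·0.3·2.8·1.4) = 2.73 and power is 82%; at r = 0.5 and 0.6 it is 90% and 94%.
- **The strata are random effects.** A reader might infer this from the word mixed. The article never says so, and a mixed model also has fixed effects.
- **The Discussion sets a third primary test.** It says "we chose the same main criterion, which was NRS improved by at least 2 points", but that sentence explains the choice of effect size for the sample-size calculation.

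**Conclusion.** The point holds as a mismatch of definitions with a modest cost in precision, plus a separate wording gap in the strata. It should be corrected, but it does not threaten validity.

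The endpoint and its analysis disagree on the face of the text. Against continuous baseline adjustment, the planned model loses about 1 point of power at r = 0.3, 3.5 at r = 0.5 and 5 at r = 0.6. These figures rest on assumed correlations, on 2.8 being the SD of D8 scores, and on a roughly even split of the stratum. The trial is not underpowered against its own calculation at any of these values.

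The gap between 6 and 7 follows from the text alone. The share of patients in it, about 17–22%, rests on assumed baseline distributions.

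**What to change.** 1. In the Study objective section and the section on analysis of the primary endpoint, state one primary analysis: the between-arm difference in mean D8 NRS from a linear model with continuous baseline NRS, centre and pain stratum as fixed effects. Say that the treatment effect is the same whether D8 or change is the response.
2. Define that baseline once, and use the same baseline in the abstract, the Study objective section and the Figure 1 legend. Without this, the equivalence in item 1 does not hold.
3. In the Randomization section, define the strata so that every eligible mean has a class, for example below 7 versus 7 or above. If randomisation has begun, do not redefine them: document the rule that the system actually applied and analyse by the strata as randomised.
4. Say whether 2.8 is the SD of D8 scores or of change.

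The cost is wording, plus one stratum definition in the electronic CRF if no patient has yet been randomised. No new data are needed, and the sample size can stay as it is. The analysis wording should be fixed before unblinded data are seen.

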#### Analysis of secondary endpoints

The mean NRS score on D8 will be compared between the active tDCS arm and the sham tDCS arm using a mixed linear model in order to take stratification factors into account. This analysis will also be adjusted for analgesic consumption based on the MQS score.

The immediate efficacy of tDCS on pain intensity will be compared between the two arms using a mixed linear model with the pre- and post-tDCS difference of the NRS score as the variable to be explained. This model will take repeated measures per patient into account.

The response rate will be compared between the two arms by a mixed logistic model in order to take stratification factors into account.

The residual analgesic effect on D14 and D21 will be studied using a mixed linear model in order to take stratification factors into account. This analysis will also be adjusted for analgesic consumption.

The course of quality of life assessed by the BPI, ESAS, HADS and STAI-Y between D0 and D7 will be compared between the two arms by a mixed linear model in order to take stratification factors into account.

Analgesic consumption, evaluated by the MQS questionnaire, will be compared between the two arms using a mixed linear model.

Complementary analysis of the primary efficacy endpoint could be conducted on a per protocol population including all patients of the mITT population not presenting any major protocol violations. These major violations will be defined in the analysis plan before locking the database.

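### The immediate-effect and analgesic-consumption models are the only ones described without the stratification factors; if fitted as written, their tests may be somewhat conservative

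*Protocol article*

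**What the plan says.** In the protocol article, section Randomization, allocation "will be stratified according to the mean baseline pain intensity", in two bands, and also by centre.

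The analysis sections then describe the models endpoint by endpoint:

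- **NRS at D8** (Analysis of the primary endpoint): compared "using a mixed linear model in order to take stratification factors into account". The same phrase returns in the secondary version that also adjusts for MQS.
- **Response rate** (Analysis of secondary endpoints): "The response rate will be compared between the two arms by a mixed logistic model in order to take stratification factors into account".
- **D14 and D21**: "The residual analgesic effect on D14 and D21 will be studied using a mixed linear model in order to take stratification factors into account".
- **BPI, ESAS, HADS and STAI-Y**: these "will be compared between the two arms by a mixed linear model in order to take stratification factors into account".
- **Immediate effect of each session**: compared "using a mixed linear model with the pre- and post-tDCS difference of the NRS score as the variable to be explained", followed by "This model will take repeated measures per patient into account". Strata are not mentioned.
- **MQS**: "Analgesic consumption, evaluated by the MQS questionnaire, will be compared between the two arms using a mixed linear model". Nothing further is given in that section.

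The section Study objective adds that repeated measurements of the quantitative secondary endpoints, MQS among them, are analysed as mean variation from D0 to D21. MQS is measured at D0 (Inclusion visit; Table 1).

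**The concern.** Four endpoint descriptions name the strata and two do not. For the immediate effect, the article gives a different reason for using a mixed model, namely repeated sessions. A statistician following that sentence literally would model the within-patient structure and omit the factors used to randomize. For MQS the text leaves it open.

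Stratified randomization removes chance imbalance in the strata from the treatment estimate. A model without the strata does not credit this: it leaves between-stratum variation in the residual and reports a standard error larger than the true one. At stake are unnecessarily wide confidence intervals and tests run below their nominal level. Both outcomes are listed among the secondary objectives, and General study methodology makes lower analgesic doses one of the aims of tDCS.

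**Working it through.** **The plan's own figure.** The article gives no precision or power for these two comparisons. Its only calculation is for the primary endpoint: difference 2, SD 2.8, power 80%, alpha 5%. A two-sided t-test needs 31.76, so 32 per arm (64 in total), and 64 × 1.10 = 70.4, stated as 70. This reproduces and does not bear on the point.

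**Inputs for the check.** From the article: 70 patients, 1:1 allocation, two centres, two baseline-pain bands. Assumed: the share R² of outcome variance explained by the strata, taken from 0 to 30%; for the simulation, also equally likely strata, permuted blocks of 4, and one value per patient. For the immediate-effect model, with complete sessions, read R² as a share of the variance of the patient's mean before/after difference, because treatment varies between patients.

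**Formulas.**
- Reported SE without strata ÷ SE with strata = 1/√(1 − R²)
- Real type I error without strata = 2[1 − Φ(1.96/√(1 − R²))]
- For an effect with nominal 80% power (1.960 + 0.842 = 2.802): actual power without strata = Φ(0.842/√(1 − R²)); with strata = Φ(2.802/√(1 − R²) − 1.960)

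| R² | SE ratio | Type I error without strata | Power without / with strata |
|---|---|---|---|
| 0 | 1.000 | 5.0% | 80.0% / 80.0% |
| 0.05 | 1.026 | 4.4% | 80.6% / 82.0% |
| 0.10 | 1.054 | 3.9% | 81.2% / 84.0% |
| 0.20 | 1.118 | 2.8% | 82.7% / 87.9% |
| 0.30 | 1.195 | 1.9% | 84.3% / 91.8% |

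**Simulation** (4,000 trials per row, no treatment effect, outcome SD 1):

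| R² | True SD of estimate, without / with strata | Mean reported SE, without / with | Rejection rate, without / with |
|---|---|---|---|
| 0 | 0.2411 / 0.2412 | 0.2378 / 0.2379 | 5.25% / 5.53% |
| 0.10 | 0.2252 / 0.2246 | 0.2388 / 0.2265 | 3.75% / 4.57% |
| 0.20 | 0.2135 / 0.2127 | 0.2386 / 0.2128 | 3.05% / 4.98% |
| 0.30 | 0.2011 / 0.1994 | 0.2390 / 0.1996 | 2.13% / 4.93% |

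The true spread is nearly the same either way; only the reported SE moves. At R² = 0.30 the ratio is 0.2390/0.1996 = 1.197, in line with the formula. At R² = 0, including the strata costs practically nothing (0.2379 against 0.2378).

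**D0 MQS as covariate or change score.** With equal variances at D0 and follow-up and correlation r (assumed), the variance is proportional to 2(1 − r) for a change score and to 1 − r² for a D0-adjusted analysis. The ratio is (1 + r)/2, so the reduction is (1 − r)/2:
- r = 0.5: 25%
- r = 0.6: 20%
- r = 0.7: 15%

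These reductions should not be added to the gain from the strata, because D0 MQS may itself differ by centre and pain band and the two overlap.

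**The case against.** The strongest reply is that silence is not exclusion. The article lists the full terms of no model, it refers to an analysis plan that is not shown, and covariates of secondary models are often settled there. This has most force for MQS: elsewhere in the analysis sections the strata are usually the stated reason for a mixed model, so they may well be intended. A reader might infer that the plan deliberately drops the strata from both models; the document does not say so. What stands is that the article does name the strata model by model, and that these two descriptions differ.

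A reader might also infer that the two estimates become less precise or biased. Neither follows. The simulated spread is practically unchanged, and the error is in the conservative direction. Power without strata does not drop below its nominal value either; what is lost is the gain that the design makes available.

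The size is uncertain. The article gives no variance share for the strata, and a within-session difference already subtracts much of the pain level, so the gain there may be small. R² near 0 gives none.

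On the baseline covariate, no model in the analysis sections names its own D0 value, not even the primary one, so these two are not out of line in that respect. A reader might compare with an analysis of D8 MQS alone, where the variance reduction would be r², or 25 to 49% over the same correlations. That comparator is weak, because Study objective describes an analysis of change from D0. Both a change score and a D0-adjusted analysis are unbiased under randomization, so the choice is one of efficiency.

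**Conclusion.** The point holds as a minor one. The immediate-effect and MQS models are the only ones described without the stratification factors. Fitted as written, with prognostic strata, they would report standard errors 0 to just under 20% too large and test at a real level between 5% and about 2%, for an assumed 0 to 30% of variance explained. Power forgone for an effect with nominal 80% power ranges from nothing to 7.5 percentage points (91.8 − 84.3). Using D0 MQS as a covariate in place of a change score would cut variance by a further 25 to 15% at most, for assumed correlations of 0.5 to 0.7. None of these ranges comes from the document. There is no bias and no excess of false positives. Only two secondary analyses are touched; the primary analysis and the 70 patients stand.

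**What to change.** In Analysis of secondary endpoints, or in the analysis plan before the database is locked:

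- State that centre and baseline-pain stratum enter both the immediate-effect model and the MQS model.
- Analyse follow-up MQS with D0 MQS as a covariate, instead of relying only on change from D0.
- Mean baseline NRS may be added to the immediate-effect model. The pre-session scores of sessions 2 to 5 should not be covariates: they are measured after randomization and could absorb part of the treatment effect.

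The cost is a sentence or two of text. No new data, visits or patients are needed, and if the strata explain nothing the loss of precision is negligible.
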